### Treatment adherence and discontinuation

Patient adherence to RT and PBMT will be monitored. While interruptions are not initial exclusion criteria, discontinuation is defined as:

RT discontinuation: Cessation before the full dose (medical decision or refusal). Such participants will be excluded from follow-up;PBMT discontinuation: missing two or more consecutive sessions or complete intervention cessation, including missed appointments or loss to follow-up, will not result in exclusion from the study. These participants will be treated in the analysis according to the intention-to-treat (ITT) principle, with all data collected up to the time of withdrawal included in the analyses. Withdrawal from PBMT will be recorded as an adherence variable, allowing for an exploratory analysis of the relationship between the number of sessions completed and clinical outcomes. A per-protocol analysis, including only participants who completed at least 80% of the scheduled PBMT sessions, will be performed as a sensitivity analysis to verify the robustness of the results obtained in the ITT analysis.

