### Secondary outcomes

Compare IO and TC PBMT regarding:

OM severity (NCI-CTCAE);Pain intensity (NRS);Ulcerated area extension (grades 2–4) will be registered with digital images;Treatment interruptions (unplanned RT/CRT modifications);Unscheduled healthcare utilization (emergency visits or hospitalizations due to OM complications).

This study explores PBMT delivery routes to standardize application parameters and optimize supportive care for patients with head and neck malignancies.

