### Statistical analysis

Analyses will be performed using Jamovi software (version 2.6.44). Normality will be assessed using the Shapiro-Wilk test, and variables will be described using frequencies and percentages (categorical variables) or means, standard deviations, and medians with interquartile ranges (continuous variables). Baseline comparability between groups will be assessed using Student’s t-test or the Mann-Whitney U test (continuous variables) and the chi-square test or Fisher’s exact test (categorical variables).

The primary outcome, oral mucositis severity (WHO scale), will be analyzed longitudinally using a mixed-effects ordinal logistic regression model to account for the repeated measurements. The model will include treatment group, assessment time, and the treatment vs. time interaction as fixed effects, with participant included as a random effect to account for within-subject correlation. Total radiotherapy dose, tumor location, and concomitant chemotherapy will be included as covariates.

Pain intensity (NRS) will be analyzed longitudinally using an appropriate mixed-effects regression model according to its distribution. The primary analysis will follow the intention-to-treat principle. Missing outcome data will not be imputed; instead, the mixed-effects ordinal logistic regression model will incorporate all available repeated measurements and account for incomplete observations over time under the assumption that data are missing at random.

The primary objective is to determine whether transcutaneous infrared PBMT is non-inferior to intraoral red PBMT regarding oral mucositis severity. Non-inferiority will be assessed using the estimated treatment effect obtained from the longitudinal mixed-effects model and interpreted according to the prespecified non-inferiority margin of 0.5 WHO grade.

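### Ending follow-up for participants who stop radiotherapy early conflicts with the intention-to-treat analysis, and may favour non-inferiority if the transcutaneous arm is truly worse

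*Protocol article*

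**What the plan says.** The protocol article, under Treatment adherence and discontinuation, gives two different rules.

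- **Stopping RT:** "RT discontinuation: Cessation before the full dose (medical decision or refusal). Such participants will be excluded from follow-up".
- **Stopping PBMT:** this, "including missed appointments or loss to follow-up, will not result in exclusion from the study". These participants are analysed by intention-to-treat, "with all data collected up to the time of withdrawal included in the analyses".

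Temporary RT interruptions are treated separately: "While interruptions are not initial exclusion criteria".

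Under Statistical analysis: "The primary analysis will follow the intention-to-treat principle". On missing data: "Missing outcome data will not be imputed; instead, the mixed-effects ordinal logistic regression model will incorporate all available repeated measurements", under a missing-at-random assumption. The model adjusts for RT dose: "Total radiotherapy dose, tumor location, and concomitant chemotherapy will be included as covariates".

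Under Secondary outcomes, the arms are also compared on "Treatment interruptions (unplanned RT/CRT modifications" and on emergency visits or hospitalisations due to mucositis.

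**The concern.** Intention-to-treat means that randomised participants are followed and analysed whatever happens to their treatment. A rule that ends follow-up after a post-randomisation event does not fit that principle. It is also less protective than the rule a few lines later for participants who stop PBMT.

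The triggering event need not be independent of the outcome. The Introduction says that pain and dysphagia from mucositis often interrupt RT. Cessation can come from a medical decision or a refusal, and the trial is open-label, so knowledge of the arm can enter either one. If TC controls mucositis less well, more TC participants might stop RT, and their later, possibly severe, grades would never be recorded. That would favour a false claim of non-inferiority, the error this design most needs to avoid. Mucositis-related healthcare use after cessation would be lost as well, and a model for WHO grade cannot recover it.

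**Working it through.** **1. The passages side by side**

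| Event | Stays in follow-up? | Earlier data stated as kept? |
|---|---|---|
| Temporary RT interruption | Yes | Not an issue |
| PBMT discontinuation | Not excluded from the study | Yes |
| RT cessation before full dose | No | Not stated |

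Two readings of the last row are possible: (A) grades recorded before cessation stay in the model, as the sentence on all available measurements suggests; (B) the participant is removed altogether.

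**2. The plan's own figures**

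The margin is 0.5 WHO grade, one-sided alpha 0.025, power 80%, attrition 10%, 27 per arm. No standard deviation is given, so 27 cannot be reproduced directly. Solving for it with n = 2 × SD² × (1.960 + 0.842)² / 0.5², an SD of 0.618 gives n = 24, and 24 / 0.9 = 26.7, rounded up to 27. The 10% allowance is 0.10 × 27 = 2.7 participants per arm, from all causes. With an assumed SD of 0.62, power is 0.842 at 27 evaluable per arm, 0.798 at 24, 0.763 at 22 and 0.722 at 20. Under reading B, losses beyond the allowance therefore also cost power.

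**3. Illustrative simulation of the bias**

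Assumed inputs: 21 visits (35 fractions / 5 per week = 7 weeks, × 3 sessions), WHO grade 0 to 4, chance of stopping RT rising at grades 3 and 4, 4000 to 6000 participants per arm, and a linear mixed model as a stand-in for the planned ordinal model. Bias = TC minus IO (intraoral) difference estimated from retained data, minus the same difference from complete data. A negative value favours non-inferiority.

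Mucositis-driven stops, TC truly worse:

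| Handling | Stopping, IO / TC | Complete data | Retained data | Bias |
|---|---|---|---|---|
| A, stop depends on recorded grade | 11% / 22% | 0.476 | 0.476 | 0.000 |
| A, same | 9% / 30% | 0.773 | 0.772 | −0.001 |
| A, grade at the stop unrecorded | 10% / 22% | 0.511 | 0.499 | −0.012 |
| A, same | 10% / 32% | 0.771 | 0.755 | −0.016 |
| B, participant removed | 4% / 10% | 0.469 | 0.438 | −0.031 |
| B, same | 5% / 16% | 0.785 | 0.722 | −0.063 |
| B, same | 10% / 23% | 0.508 | 0.412 | −0.096 |
| B, same | 10% / 32% | 0.779 | 0.640 | −0.139 |

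With truly equal arms, or with stops unrelated to mucositis, there was no material bias under either reading.

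**4. Against the margin**

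- Reading A: at most about 0.02 / 0.5 = 4%.
- Reading B, higher stop rates: 0.10 / 0.5 = 20% to 0.14 / 0.5 = 28%. In one row a difference just beyond the margin (0.508) falls inside it (0.412).
- Reading B, lower stop rates: 0.03 / 0.5 = 6% to 0.06 / 0.5 = 12%.

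The higher rates mean 0.23 × 27 = 6.2 to 0.32 × 27 = 8.6 TC participants stopping RT, well above the 2.7 all-cause dropouts the plan allows for.

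**5. The planned sensitivity analysis**

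The per-protocol set requires at least 80% of scheduled PBMT sessions. PBMT is given during RT, so if sessions are counted against the planned course, early RT stoppers tend to fail this threshold too. The check then drops the same people and does not test the missing-at-random assumption.

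**The case against.** A reader might infer that patients whose mucositis ends RT vanish from the primary outcome and that the comparison therefore leans towards non-inferiority. The document does not support that.

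- The rule removes participants from follow-up, not expressly from analysis. The model uses all available measurements, and WHO grade is recorded at each visit, so grades leading up to cessation would normally remain.
- The Introduction links mucositis to temporary interruption of RT, and interruptions do not trigger the exclusion. How often mucositis ends RT permanently is not stated.
- The direction is conditional. With equal arms or unrelated stops there is no lean, and more mucositis-driven stops in IO would push the other way.

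A larger size is also tempting. If 3 of 27 TC participants stop at grade 4, none stop in IO, and the rest average grade 2, the later TC mean is understated by 3/27 × 2 = 0.22 grade, or 44% of the margin. That is a raw mean of later visits, not the planned mixed model, and it assumes grade 4 persists after RT ends. The plan's 10% attrition covers all causes in both arms and does not support a 3-versus-0 split.

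On the dose covariate, a reader might infer adjustment for delivered dose, which cessation shortens. But Clinical and treatment-related variables uses total dose for the prescribed regimen, so prescribed dose is the natural reading. Only a clarification is needed.

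It is also fair that missing-data sensitivity analyses are commonly left to an analysis plan that is not shown. What stands is the stated rule: it conflicts with intention-to-treat, leaves the earlier data unaddressed, and no later analysis can recover assessments never made.

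**Conclusion.** The contradiction is real and should be resolved. The rule may create outcome-related missing data, and may bias the comparison towards non-inferiority if TC is truly worse and causes more RT cessations. On the assumed inputs the bias is negligible (about 0 to 0.02 grade) if data up to cessation stay in the mixed model. It is about 0.10 to 0.14 grade, 20% to 28% of the margin, if these participants are removed entirely at the higher assumed stop rates, and 0.03 to 0.06 at the lower ones. These sizes rest on assumed stopping behaviour and a linear stand-in model, so they show the range rather than predict this trial. The practical point is that the text leaves open which reading applies, and the size of the bias depends mainly on that.

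**What to change.** In Treatment adherence and discontinuation, delete the sentence that ends follow-up for RT stoppers. Then state:

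1. WHO, NCI-CTCAE, pain and healthcare-use assessments continue to the planned end of RT for all randomised participants, unless consent is withdrawn.
2. All data before and after RT cessation enter the intention-to-treat analysis.
3. One sensitivity analysis for mucositis-related RT cessation departs from missing at random, for example by shifting unobserved post-cessation grades upwards over a stated range.
4. The total radiotherapy dose covariate is the prescribed dose.

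This changes data collection and analysis only, not any treatment decision. The cost is a few sentences, some extra assessments in a handful of patients and one additional analysis. The result may be slightly less favourable to TC. The change should be made while participants are still under follow-up, because missed assessments cannot be recovered.

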Oral mucositis (OM) is the most common and challenging complication of radiation therapy or chemoradiotherapy (CRT) in patients undergoing cancer treatment, most commonly found in nearly 100% of patients undergoing high-dose chemotherapy and hematopoietic stem cell transplantation and in 75% to 90% of patients treated for head and neck malignancies [10, 11, 12, 13, 14]. Complications such as painful mouth ulcers and difficulty eating or swallowing are characteristic of OM. The pain and severe dysphagia resulting from OM can lead to significant weight loss in the patient, with a general worsening of their overall condition, and often cause temporary interruption of radiation therapy, which has been shown to reduce its efficacy [14, 15].

In this context, photobiomodulation therapy (PBMT), also known as low-level laser therapy, has emerged as an important adjunctive tool in the prevention and management of OM [16, 17]. PBMT uses light in the red and near-infrared wavelength ranges to modulate cellular processes without causing thermal damage to tissues. The light is absorbed primarily by mitochondrial cytochrome c oxidase and light-sensitive ion channels, triggering increased ATP production, controlled release of reactive oxygen species and nitric oxide, as well as modulation of intracellular calcium [18, 19, 20]. These events activate transcription factors related to cell survival, proliferation, migration, and the synthesis of new proteins, resulting in anti-inflammatory, analgesic, and tissue repair effects [18, 19, 20, 21, 22]. In contexts of oxidative stress, such as during RT, PBMT tends to reduce oxidative stress and inflammation, while simultaneously stimulating mucosal regeneration [19, 21, 22].

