### Standard supportive care protocol

All participants will receive standardized oral care per MASCC/ISOO guidelines [17]. This supportive regimen, implemented uniformly across both study arms, includes professional oral hygiene protocols, weekly dental assessments, supervised use of non-alcoholic mouthwashes, and systematic lip hydration.

Upon clinical diagnosis of ulcerative OM, localized therapeutic PBMT (660 nm, 2 J/spot, 100 mW, 20s, 20.41 J/cm²) will be initiated until complete repair [30]. When a preventive application point coincides with an ulcerated region, therapeutic irradiation will replace the preventive dose at that point. Total therapeutic sessions and cumulative energy will be recorded as potential confounders.

Procedures follow safety standards and manufacturer recommendations, including wavelength-specific protective eyewear for patients and operators. To prevent cross-contamination, handpieces will be disinfected with 70% isopropyl alcohol and covered with disposable PVC film.

Although PBMT is low-risk, participants will be monitored for adverse effects, (e.g., transient discomfort, thermal sensation, or erythema). Any event will be documented, and therapy will be discontinued if reported or observed.

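### Participants who stop radiotherapy early leave follow-up, which does not fit the intention-to-treat statement and loses later outcomes, although the likely bias in the primary comparison is small

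*Protocol article*

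**What the plan says.** Treatment adherence and discontinuation in the protocol article sets two rules.

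- RT discontinuation: "Cessation before the full dose (medical decision or refusal). Such participants will be excluded from follow-up".
- PBMT discontinuation, "including missed appointments or loss to follow-up, will not result in exclusion from the study". These participants are analysed by ITT, "with all data collected up to the time of withdrawal included in the analyses".

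Grammatically, the second rule's retention wording covers PBMT stoppers only. Temporary RT interruptions are not grounds for exclusion under the same section.

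Statistical analysis states: "The primary analysis will follow the intention-to-treat principle". It uses all available repeated measurements without imputation, to "account for incomplete observations over time under the assumption that data are missing at random".

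On the link between mucositis and RT, the Introduction says that pain and severe dysphagia from mucositis "often cause temporary interruption of radiation therapy". Secondary outcomes lists "Treatment interruptions (unplanned RT/CRT modifications", and also emergency visits or hospitalisations due to mucositis. Randomization and blinding describes the trial as open-label.

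**The concern.** ITT needs outcomes from everyone randomised, whatever happens to treatment afterwards. Here one class of randomised participants leaves observation because of an event after randomisation. The trial's own outcome list treats RT disruption as something the arms might affect. Participants also know their allocation, so refusal of further RT could differ between arms.

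If the transcutaneous (TC) arm were truly worse than the intraoral (IO) arm, and more of its participants stopped RT while badly affected, their later grades and hospital contacts would be missing mainly from that arm. The observed difference would shrink. In a non-inferiority trial that error favours the hoped-for conclusion. The rule governs data collection, so a later analysis cannot repair it.

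**Working it through.** **Inputs.** Margin 0.5 WHO grade, 27 per arm, and 10% predicted attrition (Sample size). PBMT three times a week for up to 35 fractions at five a week (Clinical and treatment-related variables) gives 7 weeks × 3 = 21 visits. The article gives no RT stopping rate, so every size below is illustrative. As a yardstick, 10% attrition is 0.10 × 27 = 2.7 participants per arm, from all causes.

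**Step 1: the text.** Set side by side, the two discontinuation rules differ: PBMT stoppers are expressly kept under ITT, and RT stoppers are not mentioned there. The ITT statement in Statistical analysis has no exception. The passages do not fit together, but the RT rule speaks of follow-up and does not mention analysis.

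**Step 2: data cut at the stop, pre-cessation grades kept.** An assumed ordinal trajectory was simulated over 21 visits. The TC deficit sat in 25% of patients, and the stopping hazard was 2% or 4% per visit at grade 3 or more. This made 13–23% of TC and 9–17% of IO participants stop, each losing 5–6 of 21 visits.

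- True late difference: 0.41 grade.
- Observed visits only: 0.39 and 0.37.
- Shift: 0.41 − 0.39 = 0.02 and 0.41 − 0.37 = 0.04, or 4% and 8% of the margin.
- Same effect in all patients: 0.50 becomes 0.495–0.50, which is negligible.

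A second simulation let the difference grow over time in all patients and pooled the raw means over all visits:

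| Hazard per visit at grade ≥3 | Stop, IO | Stop, TC | True difference | Cut at stop | Shift |
|---|---|---|---|---|---|
| 0.01 | 1.6% | 5.1% | 0.485 | 0.474 | 0.011 |
| 0.03 | 4.7% | 14.5% | 0.483 | 0.450 | 0.033 |
| 0.05 | 7.5% | 22.5% | 0.475 | 0.426 | 0.049 |
| 0.10 | 13.3% | 38.6% | 0.487 | 0.394 | 0.093 |

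The 0.03 row averages (4.7 + 14.5)/2 = 9.6% stopping, near the predicted attrition; its shift is 0.033/0.5 = 7% of the margin. The last two rows average 15% and 26%, well above it. A pooled mean under-weights the late visits that are cut, where the gap is widest. A model containing time deals with that part, which is one reason why the second simulation shows a shift under a common effect and the first hardly does.

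Both simulations use raw means. Neither fits the planned mixed ordinal model, which would recover part of the loss if data are missing at random.

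**Step 3: the stricter reading, stoppers removed wholly.** If k of 27 patients at grade g leave one arm whose other patients average m, the arm mean falls by (k/27) × (g − m).

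- k = 2: from (2/27)(3 − 2) = 0.07 to (2/27)(4 − 1) = 0.22 grade, 15–44% of the margin.
- k = 3: from (3/27)(1) = 0.11 to (3/27)(3) = 0.33 grade, 22–67% of the margin.

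This takes all losses from one arm. In the first simulation, removing stoppers from both arms turned 0.41 into 0.37–0.33.

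**Step 4: events.** Emergency visits and hospitalisations after cessation are not collected under the rule. A WHO-grade model cannot restore them.

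**The case against.** Much of the case on the other side stands.

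- **Exclusion from follow-up is not exclusion from analysis.** A reader might infer that the worst patients vanish from the primary analysis and that ITT is certainly not delivered. The article does not say so. The model takes all available measurements, so the more natural reading is that grades before cessation stay in. The figures in Step 3 belong to a reading that the text permits but does not state.
- **The link to mucositis is partly inferred.** The Introduction speaks of temporary interruption, which does not trigger the rule. That mucositis also leads to permanent cessation is reasonable, but nowhere stated.
- **Missing at random may partly hold.** If stopping depends on recorded WHO grades, the planned model handles much of it. This does not settle the matter: pain is a mechanism that the Introduction names, and pain is not in the WHO model. Worsening after the last visit is not recorded either. The one stated sensitivity analysis (at least 80% of PBMT sessions) does not test the assumption.
- **The interruption outcome is not necessarily lost.** Cessation is known when it happens and could be counted. The article simply does not say that it is.
- **Grades after RT stops may reflect recovering mucosa.** The primary outcome concerns patients undergoing RT or chemoradiotherapy, so later grades could dilute a difference between arms. This is a fair reason for a sensitivity analysis, not for collecting nothing.

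A reader might also see a conflict with Standard supportive care protocol, where treatment of ulcers "will be initiated until complete repair". That sentence describes care, whereas the exclusion concerns trial follow-up. Ending data collection does not say that care ends, so no contradiction is shown.

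**Conclusion.** The point holds in a limited form. The RT rule does not fit the unreserved ITT statement, gives RT stoppers none of the assurance given to PBMT stoppers, and ends observation on a post-randomisation event that may be related to the outcome.

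If data before cessation stay in the model, the shift in the primary comparison is likely small: about 0.02–0.04 grade (4–8% of the margin) in the first simulation, a similar 0.033 in the second at about 10% stopping, and near zero in the first when the effect is uniform. These sizes rest on assumed trajectories, assumed stopping rates and raw means. Higher stopping, or more of it in one arm, would make them larger.

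The firm loss is of WHO grades, emergency visits and hospitalisations after cessation, in any participant who stops. The case for acting is that uncollected data cannot be recovered and the remedy is cheap. It does not rest on a demonstrated large bias.

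**What to change.** Replace the RT-discontinuation sentence so that:

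1. participants who stop RT early stay in the ITT set with all their data;
2. WHO, NCI-CTCAE and pain (NRS) scores, emergency visits and hospitalisations continue to be collected on the common visit calendar to the date on which RT was planned to end;
3. the reason for stopping is recorded and reported by arm;
4. permanent RT cessation counts as an event in the treatment-interruption outcome.

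Add a sensitivity analysis that uses only visits during RT, because later grades may reflect recovering mucosa.

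The change concerns data collection and analysis only and leaves RT, PBMT and supportive care as they are. It costs a short amendment and a few extra outcome visits for a small number of participants.
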